### Study objective

The aim of this randomized controlled trial is to compare one novel, personalized TKR implant design (Persona CR, Zimmer, Warsaw, IN, USA) against two conventional TKR design (PFC CR,DePuy, Warsaw, IN, USA and NexGen CR, Zimmer, Warsaw, IN, USA) in terms of functional outcome and cost-effectiveness.

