### Primary and secondary outcome measures

The primary outcome is the Finnish language version of the OKS (33) measured both preoperatively**,** and postoperatively at 2–3, 12, and 24 months. The OKS is a validated and reliable PROM. The questionnaire comprises 12 items regarding pain and activities of daily living (ADL) specifically related to the knee. Each item is scored on a five-level Likert scale 0 (worst disability) to 4 (no disability). The total score can range from 0 to 48, with 48 being the best possible score. The minimal clinically important difference (MCID) depends on the purpose of the comparison: it has recently been defined as 5 points, when different patient cohorts are compared against each other [18, 30, 33, 34]. Thus, in this study, a > 5-point difference in median OKS at 24 months postoperatively between any of the three cohorts studied (Persona CR, PFC CR, and NexGen CR) will be defined as a clinically significant difference in functional outcome.

The secondary measured outcomes both preoperatively, and after surgery at 2–3, 12, and 24 months are the FJS, the 15D, the UCLA activity score, and the VAS pain scale.

The FJS is an assessment tool designed especially for well-performing patients and describes the patients’ ability to forget the artificial joint in everyday life. The questionnaire comprises 12 items regarding and integrating pain, stiffness, function in ADL, patients’ activity levels, and psychosocial factors. Each item is scored on a five-point Likert response format of 1 (never) and 5 (mostly), and scores are summed and linearly transformed to a 0 to 100 scale. The high scores indicate good outcome, equaling a high degree of forgetting the replaced joint during ADL [17, 22, 35]. The validity and reliability of the FJS has been reported to be good, with a lower ceiling effect than the OKS [36].

The 15D is a generic, comprehensive (15-dimensional) self-administered instrument for measuring health-related quality of life (HRQoL)(19). The questionnaire comprises 15 dimensions with 5 ordinal levels on each dimension. From each dimension, the respondents choose the level that best describes their present health status. A set of population-based preference and utility weighs is used to generate the 15D score on a 0 (being dead) to 1 (full health) scale. Moreover, the 15D scores are generalizable and valid for deriving quality-adjusted life years (QALYs). The generic MCID for the change of 15D scores are ±0.15 [19, 37].

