### Patient randomization

When TKR surgery is decided, the eligible patients will be informed and those willing to participate will be randomized into one of the three implant groups. Block randomization lists will be computer-generated. Block-size will be variable with equal allocations to the three study groups. Numbered, sealed envelopes will be prepared. The trial coordinator will open the next (in number) sealed randomization envelope pre-operatively and reveal allocation. Opening of the envelope will be done after the surgeon has ascertained that the patient meets the eligibility criteria and that all of the implant types are feasible for the patient. The allocated implantation will then be performed, and the envelope, with study number indicated, returned to the trial coordinator.

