### Statistical methods

Descriptive statistics, including mean and standard deviation, for continuous variables will be used. Differences between groups in continuous skewed main outcome variables will be analyzed using the Mann-Whitney U-test, and t-test when variables are normally distributed. Results will be presented with 95% confidence intervals. Two-way-tables with the chi-square test will be used for dichotomous variables, and multivariate analysis will be conducted with regression analysis. The α-level will be set at 0.05. SPSS Statistics version 23 (IBM Corp., Armonk, NY) will be used for the analysis.

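### Three arms are compared on the 24-month OKS with two-sample tests at one undivided 0.05: tested pair by pair, the chance of at least one false p<0.05 is about 12% (9% for the two Persona pairs), and the tie to the 5-point rule is not stated

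*Protocol article*

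**What the plan says.** Four places in the protocol article bear on this.

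- **Primary and secondary outcome measures.** Clinical significance is defined as "a > 5-point difference in median OKS at 24 months postoperatively" "between any of the three cohorts studied", with Persona CR, PFC CR and NexGen CR listed. Three named arms make three pairs. The sentence sets a threshold for clinical importance and contains no p-value.
- **Statistical methods.** "Differences between groups in continuous skewed main outcome variables will be analyzed using the Mann-Whitney U-test, and t-test when variables are normally distributed". The same section adds: "The α-level will be set at 0.05". Both tests compare two groups. No three-group test, order of comparisons or adjustment is given. Regression is mentioned only for multivariate analysis.
- **Study objective.** The aim is to "compare one novel, personalized TKR implant design" with two conventional ones. That makes two pairs and leaves out PFC versus NexGen.
- **Sample size.** The Forgotten Joint Score (FJS) calculation is for one two-group comparison at alpha 0.05 and power 0.8, with delta 13 and SD 25. For the OKS only the result is printed, 48 per arm.

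Allocation is equal (Patient randomization: "Block-size will be variable with equal allocations to the three study groups").

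**The concern.** A two-sample test cannot compare three arms in one step. With only such tests named, a search over any pair means two or three tests on the primary outcome. One undivided alpha then does not describe the chance of a false significant result for the primary question as a whole.

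The article also gives two different comparison families: three pairs in the outcome section and two in the objective. A significant PFC versus NexGen result would count as a primary finding under one and fall outside the aim under the other.

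The first hypothesis expects similar OKS results across the designs, and the article stresses that the novel design costs substantially more. A chance p<0.05 in one pair could be reported as an implant difference in either direction, with a stated error rate of 5% that does not apply to it.

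**Working it through.** **Inputs.** Alpha 0.05, two-sample tests, three equal arms, 80 per arm and 10% drop-out (from the article), so 80 × 0.9 = 72 evaluable per arm. Two-sided testing is assumed, because sidedness is not stated. The article gives no SD for the OKS, so every OKS distribution below is an assumption.

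**1. The plan's own figure.** For delta 13, SD 25, two-sided 0.05 and power 0.80:

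n = 2 × (1.960 + 0.842)² × (25/13)² = 2 × 7.849 × 3.698 = 58.05, so 59 per arm. The exact t-test solution is 59.03, so 60.

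The printed figure is 64. It is reproduced at delta 12.5, half an SD (t-test 63.8, so 64), and 64/0.8 = 80 gives the arm size. The mismatch is on the safe side and is a separate matter. What counts here is that the calculation uses an undivided 0.05 for one pair of arms.

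**2. Chance of at least one p<0.05 when all arms are equal.**

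- Three pairs: some |Z| exceeds 1.96 exactly when the studentized range of three means exceeds 1.96 × √2 = 2.772. P(Q > 2.772; 3 groups) = 0.122.
- Two Persona pairs: the two statistics share an arm and correlate at 0.5. The bivariate normal gives 1 − P(both |Z| ≤ 1.96) = 0.091.
- Treating three pairs as independent would give 1 − 0.95³ = 0.143, which is too high because pairs share arms.
- Simulation check with Mann-Whitney on a rounded, skewed 0–48 score (scaled beta, mean 39, SD 8.65, 72 per arm, 10,000 runs): 12.0% for three pairs and 9.0% for two.

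**3. The same null with the 5-point rule added.** In that simulation, at least one median gap exceeded 5 points in 1.1% of runs. A gap above 5 points together with p<0.05 in the same pair occurred in 0.9%. Other assumed distributions, with 80 per arm and both conditions required:

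| Assumed OKS distribution | False-claim rate |
|---|---|
| Skewed, SD 6.6 | 0.04% |
| Normal, SD 8 | 0.5% |
| Normal, SD 10 | 2.1% |
| Normal, SD 12 | 4.9% |

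**4. Error rate with a global test first.** With Kruskal-Wallis at 0.05 before any pairwise test, the chance of at least one significant pair was between 4.6% and 5.2% across separate simulations (5.0% in the run of step 2). The logic is exact for three groups. If the global null is false, at most one pair can still be equal, so testing pairs at 0.05 adds no further inflation.

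**5. Power for the FJS inputs** (delta 13, SD 25, so 0.52 SD; 72 evaluable per arm):

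| Rule | Power for a pair differing by 13 points |
|---|---|
| Unadjusted, 0.05 | 87% |
| Global F-test first, Persona differing equally from both others | about 85% |
| Global F-test first, third arm midway | about 79% |
| Bonferroni, 0.05/3 | 76% |

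**The case against.** The strongest objection is that the outcome sentence is not a significance rule. It defines clinical importance by a median gap of more than 5 points, and identical arms rarely produce such a gap: about 1% of trials under the skewed model with SD 8.65. This stands. A reader might infer that the trial has a 12% chance of falsely declaring a clinically important implant difference. The article does not support that reading, because 12% is the rate of at least one p<0.05 whatever the size of the gap. But neither does it say that a claim needs both the test and the gap.

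Second, testing each pair at 0.05 is inferred; the article does not say that alpha applies per comparison. That is fair, but two-sample tests with one undivided alpha suggest no other reading, and the two-pair reading still gives 9%.

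Third, a condensed article may leave multiplicity to a statistical analysis plan that is not shown. A correction may exist there, and its absence here would not be a finding by itself. What remains is what the article does fix: tests that cannot take three arms at once, one alpha, and two comparison families that disagree.

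Fourth, the authors expect similarity and worry about type 2 error, and a global test makes significance harder to reach. This is a real trade-off. Step 5 shows that it costs a few points of power, and a non-significant result would not establish similarity under either rule.

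**Conclusion.** The point holds as a should-fix. As written, pairwise testing of the 24-month OKS gives about a 12% chance of at least one p<0.05 among identical arms for three pairs, and about 9% for the two Persona pairs, against a stated 5%. These two figures rest on two-sided tests, equal arms and no adjustment elsewhere. They hardly depend on the OKS distribution.

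The rate of false claims that also pass the 5-point gap does depend on it: from well under 1% to about 5% over the assumed distributions with SDs of 6.6 to 12. The article leaves open which of these rates applies, because it never joins the test to the threshold. That gap, together with the two comparison families, is what needs settling.

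**What to change.** For the 24-month OKS:

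1. Test the three arms together at 0.05 (Kruskal-Wallis, or ANOVA if normally distributed). Do pairwise tests at 0.05 only if that test is significant.
2. Name Persona versus PFC and Persona versus NexGen as the primary pairs, and PFC versus NexGen as secondary, so that the outcome section agrees with the objective.
3. State that a claim of an implant difference needs both the gated test and the median gap of more than 5 points, or say which of the two governs.
4. Restate power under this rule, and print the OKS delta and SD.

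The cost is wording and some power per pair: for the FJS inputs with 72 evaluable per arm, 87% falls to about 79–85%. No extra patients are needed to stay near the planned 80%. OKS power under the new rule cannot be restated from the article, because its delta and SD are not given.

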### Hypotheses

Our primary hypotheses in the study are the following:
i.The two conventional TKR implant designs and the novel implant design will yield similar functional outcomes measured with OKSii.Total knee replacement with either of the two conventional TKR implant designs will be more cost-effective than TKR with the novel implant design regarding quality-adjusted life years (QALYs) measured with the 15Diii.High pain sensitivity will be associated with poor functional outcome irrespective of the implant design or radiographic severity of knee osteoarthritis (OA).

### Patient recruitment

Patients will be recruited from Coxa’s outpatient clinic according to our inclusion and exclusion criteria. The participating orthopaedic surgeons will recruit patients alongside their routine out-patient work. Written informed consent will be obtained. In the study, the indications for surgical treatment will follow the routine clinical guidelines of the hospital (Fig. 1).

**Fig. 1 Fig1:**
[figure not shown]
Patient flow through the trial (PROM: Patient Reported Outcome Measures)

### Patient inclusion criteria

patients undergoing total knee replacement surgery for primary knee OAno previous open major surgery in the joint (e.g., osteotomy)age 50–70 yearsunilateral operative treatment with no plans for surgical treatment of the contralateral knee in the near futurepatients living in the local hospital district (Pirkanmaa Hospital District)Kellgren-Lawrence grade 3–4 knee osteoarthritis in plain radiographs

### Patient exclusion criteria

unwilling to provide informed consent> 15 degrees varus or valgus, or > 15 degrees fixed flexion deformitypredominantly patellofemoral osteoarthritisPhysical, emotional, or neurological conditions that would compromise the patient’s compliance with postoperative rehabilitation and follow-up (e.g., drug or alcohol abuse, serious mental illness, general neurological conditions, such as Parkinson, MS, etc.)

### Patient randomization

When TKR surgery is decided, the eligible patients will be informed and those willing to participate will be randomized into one of the three implant groups. Block randomization lists will be computer-generated. Block-size will be variable with equal allocations to the three study groups. Numbered, sealed envelopes will be prepared. The trial coordinator will open the next (in number) sealed randomization envelope pre-operatively and reveal allocation. Opening of the envelope will be done after the surgeon has ascertained that the patient meets the eligibility criteria and that all of the implant types are feasible for the patient. The allocated implantation will then be performed, and the envelope, with study number indicated, returned to the trial coordinator.

### Preoperative patient evaluation

The preoperative medical history will be carefully documented according to routine screening for TKR surgery. The preoperative planning will include plain radiographs of the operated knee and standing long axis radiograph of the affected limb. Specific attention will be paid to record history of chronic pain, long- standing pain medication, a history of fibromyalgia, depression, anxiety, or other mental disturbances.

In addition to our normal preoperative protocol (including OKS), the patient will be asked to complete the following questionnaires/tests: the 15 D, the UCLA activity score, the FJS, and questionnaires for pain sensitivity and brief pain inventory.

### Operative treatment

Patients will be operated upon using the implant allocated in the randomization. Perioperative treatment will be carried out according to the routine protocol of the hospital: total knee arthroplasties (TKA) will be performed using the medial parapatellar approach, and the decision to use / not to use a tourniquet will be based on the surgeon’s preference. The mechanical alignment [38] technique will be used. The measured resection [39] technique, a combination of bony landmarks (femoral epicondyles, posterior condylar axis, and anterior-posterior axis), will be used to determine proper rotation of the femoral component. Distal femoral resections will be performed first using an intramedullary guide, which will be followed by a posterior referencing cutting block used to identify the proper component size. An appropriate 4-in-1 resection block will be used to perform anterior, posterior, and chamfer bone cuts in the femur. An extramedullary alignment guide will then be used to perform the tibial cut. Soft-tissue balance will be evaluated using either directly trial components or by first assessing ligamentous and gap balance with a tenser-device. Again, this will be based on the individual surgeon’s preferences. With trial components, range of motion, ligamentous balance, as well as extension-flexion gaps will be always assessed and recorded by the operating surgeon. If necessary, soft-tissue releases and ligament balancing will be performed to balance gap differences and/or varus/valgus ligamentous balance. All components implanted will be cemented, and the patella will only be resurfaced if there is a problem with patellar tracking. The TKAs will be carried out under spinal anesthesia in combination with intravenous sedation. General anesthesia will only be used if there is a contraindication to spinal anesthesia. Immediate full weight bearing will be allowed, and all patients will be mobilized on the day of the surgery. Antithrombotic prophylaxis, with low molecular-weight heparin, enoxaparin will be administered for 3 to 4 weeks postoperatively. All details of perioperative care and possible complications will be recorded in the hospital’s electronic database in a routine manner.

A 10 g sample of synovial tissue will be obtained during surgery. The study protocol will not require any additional tissue removal during surgery.

### Postoperative follow-up

The first postoperative visit to a physiotherapist blinded to the allocation will take place at 2 to 3 months after surgery. This visit will include a routine physical examination, plain radiographs of the operated joint, and the OKS score. In addition, the screening questionnaires/tests will be repeated, as described in Table 1. All complications and re-operations of the operated knee will be recorded.

**Table 1 Tab1:** The schedule of enrollment, interventions, and assessments

	Study period					
	Enrollment	Allocation	Post-allocation			Close-out
Timepoint^a^	*-t* _*1*_	0	*t* _*1*_	*t* _*2*_	*t* _*3*_	*t* _*4*_
Enrollment						
Eligibility screen	X					
Informed consent	X					
Medical history	X					
Allocation		X				
Interventions:						
PFC CR Total knee replacement			X			
NexGen CR Total knee replacement			X			
Persona CR Total knee replacement			X			
Assessments:						
X-ray	X			X		
Pain sensitivity (PCS)	X					
Pain inventory (BPI)	X					
Oxford Knee Score (OKS)	X			X	X	X
15D	X			X	X	X
Forgotten Joint Score (FJS)	X			X	X	X
UCLA activity score	X			X	X	X
Surgeon visit	X					
Physiotherapist visit	X			X	X	X

^a^*-t*_*1*_ = baseline, *t*_*1*_ = operative treatment, *t*_*2*_ = postoperative at 2–3 months, *t*_*3*_ = at 1 year, *t*_*4*_ = at 2 years

The follow-up visits at 1 and 2-year intervals are additional to normal clinical practice. They will be performed by a physiotherapist blinded to the allocation and will include repeating the follow-up questionnaires, as shown in Table 1. All complications and re-operations of the studied knee will be recorded.

Further to the present work-flow, follow-up visits will be planned to take place at 5, 10, 13, and 16 years from the index operations to assess the mid- to long-term outcome and implant survivorship.

### Sample size

The power analyses will be calculated using both the OKS (primary outcome) and the FJS (secondary outcome). Of these, the FJS is more sensitive in differentiating patients at the upper end of the outcome scores and requires larger patient groups. With the OKS, the estimated sample size is 48 patients per arm. With the FJS in the range of 60 to 80 and a standard deviation of 25 points, the estimated sample size is 64 patients per arm (delta = 13, sd = 25, alpha = 0.05, power = 0.8). Allowing for a 10% drop-out rate and a 10% addition due to skewness in the variable distribution, the required arm size is 80. Therefore, with three comparison arms, the total number of patients recruited into the study will be 240.

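### The 64 per arm for the Forgotten Joint Score does not follow from its printed inputs, which give 59 or 60; the gap is small and conservative

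*Protocol article*

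**What the plan says.** The Sample size section of the protocol article sizes the trial on two scores. For the Oxford Knee Score (OKS, primary) it gives 48 per arm without inputs. For the FJS (secondary), which it describes as needing the larger groups, it reports that "the estimated sample size is 64 patients per arm", and gives the inputs in brackets: "delta = 13, sd = 25, alpha = 0.05, power = 0.8". It then inflates: "Allowing for a 10% drop-out rate and a 10% addition due to skewness in the variable distribution, the required arm size is 80". Three arms of 80 make 240.

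The Statistical methods section adds "The α-level will be set at 0.05" and "Results will be presented with 95% confidence intervals". It names the t-test, or the Mann-Whitney test for skewed outcomes. Allocation is equal across arms: "Block-size will be variable with equal allocations to the three study groups". No section states whether the sample size is one-sided or two-sided.

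**The concern.** The sentence prints a result and all the numerical inputs needed to check it, apart from sidedness, and the two do not agree. A difference of 13 with a standard deviation of 25 is an effect of 13/25 = 0.52. The figure of 64 per arm is the familiar t-test size for an effect of 0.50.

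This is the calculation that fixed the trial size, and the only one whose inputs are shown. The Discussion relies on the power analysis to argue that a finding of no difference could be interpreted, and the first hypothesis expects similar outcomes. What the trial was able to detect should therefore be stated correctly.

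**Working it through.** **Inputs.** From Sample size: difference 13 FJS points, standard deviation 25, alpha 0.05, power 0.80. From Patient randomization: equal allocation. Assumed: two-sided, which fits the planned 95% intervals, and a comparison of one pair of arms, which fits the named tests.

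**Attempt to reproduce 64.** Normal approximation:

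n per arm = 2 × (1.960 + 0.842)² × (25/13)² = 58.05, so 59.

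The t-test (noncentral t) at effect 0.52 gives 59.03, so 60. Neither is 64.

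**Other readings, with difference 13 and standard deviation 25:**

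| Reading | n per arm |
|---|---|
| One-sided 0.05 | 46 (normal) or 47 (t) |
| Bonferroni, two comparisons | 71 or 72 |
| Bonferroni, three comparisons | 78 or 79 |
| Three-arm ANOVA, third arm equal to one of the pair | 55 |
| Three-arm ANOVA, third arm midway | 73 |
| Mann-Whitney, efficiency 3/π (about 0.955) | 59.03/0.955 = 61.8, so 62 |
| Mann-Whitney, worst-case efficiency 0.864 | 59.03/0.864 = 68.3, so 69 |

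None gives 64. The nearest is the Mann-Whitney correction at 62. The article does not state that correction, and its own skewness allowance is added after the 64.

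**What does give 64.** An effect of 0.50 needs 63.77 by t-test, so 64. Both 12.5/25 and 13/26 equal 0.50. Solving backwards from 64 per arm at 80% power gives a difference of 12.48 with standard deviation 25, or a standard deviation of 26.05 with difference 13.

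**Power at the stated size.** With 64 per arm, difference 13 and standard deviation 25:

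13 / (25 × √(2/64)) = 2.942; 2.942 − 1.960 = 0.982; power = 83.7% (normal), or 83.1% by t-test.

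**Effect on the inflated size.** The article does not say how its two 10% allowances combine, so four ways are shown, each rounded up:

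| Inflation | From 64 | From 60 | Difference per arm |
|---|---|---|---|
| × 1.2 | 76.8, so 77 | 72 | 5 |
| × 1.1 / 0.9 | 78.2, so 79 | 73.3, so 74 | 5 |
| / 0.81 | 79.0, so 80 | 74.1, so 75 | 5 |
| / 0.8 | 80 | 75 | 5 |

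Like for like, the difference is 5 per arm, or 3 × 5 = 15 patients in total.

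**What the enrolled size delivers.** With 80 per arm less 10%, 72 are evaluable. For one unadjusted pairwise t-test with standard deviation 25, power for 13 points is 87.3%, and 80% power is reached at 11.75, about 11.8 points.

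**The case against.** The strongest defence is rounding. Half of a standard deviation of 25 is 12.5, which prints as 13 when whole numbers are used. On that reading 64 is correct and only the display is coarse. This is the most likely origin, and it stands as an explanation. It does not remove the discrepancy: the article does not say the figure is rounded, and anyone entering the printed values gets 60. Nor is it the only candidate, since 13 with a standard deviation of 26 also gives 64. Because 25 is printed twice in the section, a slip there is less likely but not excluded.

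The defence can also say that the consequence is slight, and this stands in full. The choice is between 12.5 and 13 points on a 0 to 100 scale. The error adds patients rather than removing them. The FJS is a secondary outcome, and the 48 per arm given for the OKS does not depend on this calculation. Recruitment ended in August 2018, before the article appeared, so nothing in the conduct of the trial turns on the correction.

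**Conclusion.** The sentence is wrong as written: its inputs give 59 or 60 per arm, not 64. The point is minor. It rests on a two-sided, two-sample comparison of one pair. Sidedness is not stated, but a one-sided test, at about 47, does not rescue the figure.

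Three stronger readings are tempting, and the documents do not support them. A reader might infer that the trial is underpowered. The opposite holds for the stated FJS difference, with about 83% power at 64 per arm. A reader might infer that 240 is unsound or that the target effect is unknowable. The enrolled size more than covers 13 points pairwise, and the ambiguity is about half a point or one unit of standard deviation. A reader might also want power quoted for an overall three-arm test that gates the pairwise comparisons. The protocol specifies no such test, so figures of that kind would rest on assumptions from outside it and do not belong in this correction.

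**What to change.** Keep 240 and reconcile the difference, standard deviation, power and sample size in the one sentence. The sponsor should check which inputs were used. If the difference was 12.5, print 12.5 with 64 per arm and power 0.80. If 13 and 25 are correct, print 64 per arm with power 0.83. If the standard deviation was 26, print that. State also that the calculation is two-sided, if it was.

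Add a sentence on what the enrolled size delivers for one unadjusted pairwise t-test with standard deviation 25 and 72 evaluable per arm: about 87% power for 13 FJS points, or 80% power for about 11.8 points.

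The cost is a correction to the wording. Enrolment, conduct and analysis do not change.
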